**A. OBJECTIVES**

**Primary**

1. To compare patients' perception of helpfulness in communicating with their physicians between a question prompt sheet (QPS) and a general information sheet (GIS).

**Secondary**

2. To compare caregivers' perception of helpfulness in communicating with their physicians between the QPS and the GIS.
3. To examine the level of patients' and caregivers' overall satisfaction with the consultation with the use of the QPS versus the GIS.
4. To examine physicians' views about the information material and overall satisfaction with the use of the QPS versus the GIS.

5. To explore how the use of QPS affects the average speaking time of patient or physician during the consultation visit.
6. To establish demographic and clinical predictors of patients' perception of helpfulness of a QPS
7. To examine the overall patients' preference between the QPS and GIS in an open label phase.
8. To compare the change in patient anxiety state with the use of the QPS versus the GIS.
9. To explore the factors underlying patients' preferences for the QPS or GIS.

## **B. HYPOTHESIS**

Patients will perceive the use of a question prompt sheet as more helpful compared with a general information sheet in communicating with their physicians.

## **C. BACKGROUND**

Patients with advanced disease develop peculiar physical, psychological, social and spiritual needs that require a multidimensional approach to address them^1 and an effective communication strategy becomes the fundamental backbone of this holistic intervention. Approaches that encourage patients to actively participate and ask appropriate questions during their visit are important to enhance their understanding of their illness and empower them to make important decisions regarding their medical care. Studies have shown that greater patient participation during physician-patient encounters has been linked with positive patient psychological outcomes. However, patients and family members may be uncertain about what type of questions to ask their physicians, may forget to ask certain pertinent questions, or may feel too embarrassed to ask them. Similarly, physicians may be unsure about the type and extent of information to provide their patients, when to convey them, or whom to have those conversations with. Situational factors, such as change in disease status may alter a patient's preferences for information and involvement. The use of precise communication interventions might therefore help to address some of these barriers.

Examples of strategies used to improve physician-patient communication include the provision of

an audio recording, a post encounter summary letter to the patient after the clinic visit,

providing patients with decision aids, coaching via interactive media or face-to-face, and the use of a prompt sheet. A prompt sheet is a structured list of potential questions available for the patient to ask the physician during a clinical encounter. It may help patients to obtain their desired level of information regarding their illness, assist with decision making, and facilitate the overall communication process. It may also prevent physicians from conveying unwanted information to patients which can potentially increase their level of distress.

Various versions of a prompt sheet have been developed in different fields of medicine including general medicine, geriatric medicine, gynecological and dermatological conditions, surgical patients, diabetes, and cancer. Results from their use have been variable but predominantly positive. Some studies on the use of a prompt sheet in cancer settings showed that they were well accepted by patients and providers and increased the number and specific types of questions asked during clinical encounters. On the other hand, Butow et al. in a randomized control trial of 142 cancer patients receiving either a prompt sheet or general information sheet found that the prompt sheet did not increase the number of questions asked and the patient speaking time.

Prompt sheets are not regularly used in advanced cancer or outpatient palliative care. As integration of palliative care into routine oncologic care increases, ways to ensure that patients are able to ask questions that are important to them have become more relevant. Clayton et al. in a thoroughly conducted study developed a comprehensive booklet that contained questions addressing various topics in palliative care. However, one limitation was that it was about 20 pages long containing 112 questions, and therefore impractical for routine use at a busy outpatient clinic with time constraints and where the need for brevity is paramount in the delivery of care. Hebert et al. developed and tested a question prompt among family caregivers of cancer patients and physicians regarding discussion on end-of-life issues and had positive outcomes. However, the study did not include the patients themselves. Yeh et al. administered a question prompt sheet to 30 advanced cancer patients prior to their initial outpatient clinic consultation and found that 90% of the patients perceived the sheet as helpful and relevant. The study was however limited by the lack of an attention control group.

## **D. RATIONALE**

The use of a question prompt list has been shown to improve physician-patient interaction during clinical consultations. However, there is paucity of data on its use in the palliative care setting. In an initial study, our team developed a consensus list of prompt sheet questions in a Delphi process by a panel of 21 palliative care experts in the Department of Palliative Care and Rehabilitation Medicine at the University of Texas M. D. Anderson Cancer Center. In a follow up preliminary study, we tested the sheet for its content validity in a group of patients and families and had positive patient reported outcomes. The next step is to conduct a randomized control trial comparing the QPS with a general information sheet among advanced cancer outpatients.

## **E. RESEARCH DESIGN**

### **E1. Study design and setting**

The study is a randomized-controlled trial to be conducted at the outpatient Supportive Care Center at the University of Texas MD Anderson Cancer Center. We plan to enroll 136 patients and up to 136 caregivers. Up to 20 physicians will be enrolled. Each physician may see up to 15 patients in this study.

### **E2. Participant selection**

#### **Patient participation**

##### ***Inclusion criteria***

1. Age 18 years or older
2. First outpatient consultation visit with a palliative care specialist.
3. Normal cognitive status, defined as a normal state of arousal and an absence of obvious clinical findings of confusion, memory deficits or concentration deficits, as determined by the patient's physician.
4. Ability to read and communicate in English
5. Diagnosis of advanced cancer
6. Signed written informed consent form.

##### ***Exclusion criteria***

1. Refusal to participate in the study

### **Caregiver participation**

A caregiver will be eligible for the study if he/she: i) accompanied the patient to the clinic visit, ii) is identified by the patient as someone who is actively involved in their overall care, iii) is able to read and communicate in English, iv) is willing to participate in the study and able to complete the questionnaires.

### **Physician participation**

A physician will be eligible if he/she is i) a palliative medicine specialist, ii) seeing the patient in consultation on the day of the study, iii) willing to participate in the study.

### **E3. Randomization**

Participating patients will be randomized in a double-blind fashion into one of two treatment groups: the active group will receive the QPS intervention and the control group will receive the GIS intervention. Randomization will be conducted via the Clinical Trial Conduct website developed by the Department of Biostatistics. We will randomize patients using Pocock-Simon's method and the randomization will be stratified by "physician" in order to carefully control for physicians' impact on patients' perception of helpfulness (primary endpoint).

### **E4. Blinding**

Both the QPS and GIS will be concealed in opaque envelopes that will be identical to each other. The research staff and the patient/ caregiver will be blinded to the contents of the envelopes. The physician will also be blinded to the type of written material given to the patient. We successfully conducted this blinding protocol in a similar previous study.

### **E5. Research team**

An orientation training will be organized for all research team members involved in the study in order to equip them with the necessary knowledge and expertise for the conduct of the study and also to standardize the provision of each intervention.

Figure 1. Summary of Study Design

[figure not shown]

## E6. Study Procedures

The research staff will first identify a potentially eligible candidate by screening all scheduled patient consultations on that day, and then inform and obtain a verbal consent from the attending physician for the patient's participation in the study. After the routine nurse assessment, the

research coordinator will obtain patient's written consent and then ask him/her to complete the Spielberger State Trait Anxiety Inventory (**Appendix A**), 2 questions from Cassileth Information Styles Questionnaire (**Appendix B**), and the Control Preferences Scale (**Appendix C**). The patient will then be randomized to receive either the QPS (**Appendix D**) or the GIS (**Appendix E**). It will take approximately 5 minutes to read through the QPS or GIS. The questionnaires should take about 5 minutes to complete. Caregivers accompanying patients to the clinic who are willing to participate in the study will also be asked to provide consent and will be given the same information material (either QPS or GIS). In a situation where more than one eligible caregiver is present, the one most involved in the patient's care, as determined by the patient, will be the first person to be approached. If he/she declines to participate, the next most involved caregiver identified by the patient will then be approached until there are no more eligible caregivers present.

During the patient-physician encounter, the physician will be asked to endorse question asking. Physician endorsement of question asking will be defined according to the following standardized protocol: 1) The physician asks the patient/ caregiver if they have any questions; and either 2) explains why it is important to ask questions, or 3) invites the patient/caregiver to ask questions more than once. The conversation will be recorded with a voice recorder and later transcribed. The audio-recordings will be sent via Box.com to Landmark Associates Inc. to be transcribed professionally. At the end of the consultation, the research staff who will be absent during the conversation, will ask the patient to complete the Spielberger State Trait Anxiety Inventory (**Appendix A**) again, the questionnaires assessing patients'/caregivers' views about the information material (**Appendix F**) and overall satisfaction with consultation (**Appendix G**). The questionnaires should take about 13 minutes to complete. The participating caregiver will also separately complete **Appendix F**. It should take about 5 minutes to complete. All the information materials will be collected from the participants after the consultation but those who indicate the desire to keep them will be given a copy of their forms for future use. At the end of the study, all study patients will receive a patient information booklet which also contains the GIS content. This is part of usual practice in the clinic and it will ensure that all patients get to receive identical standardized clinical care. The physician will also be asked to complete a physician assessment questionnaire (**Appendix H**) after the clinic encounter. This should take about 2 minutes to complete.

In a subsequent open label phase to be conducted during their next follow up clinic visit at the Supportive Care Center (SCC), patients who participated in the initial blinded study will now openly receive both information materials prior seeing the physician. At the end of the visit with the physician, patients will complete a questionnaire assessing their overall preference between the two information materials. (**Appendix I**) Patients who are unable to complete the questionnaire in the clinic they will be contacted over the phone within 48 hours to complete the questionnaire. The phone call will be audio-recorded. Patients will not be provided copies of this recording. This should take approximately 2 minutes to complete.

Using a qualitative methodology, we will also conduct a descriptive exploratory repeat assessment to gain a broad understanding of patients' preferences for the information materials they receive prior to their doctor visit for the purpose of improving physician-patient communication. A sub-set of 20 patients in this study will be invited to participate in individual interviews after their follow up visits. We will purposively sample to get a range of ages, genders, ethnicities, and disease types for the interviews and match these characteristics in both treatment groups. The individual interviews will be conducted in person in a private clinic room after the physician visit by an interviewer trained in qualitative techniques (see Appendix J for interview guides). Patients who are unable to complete the interview in person will be contacted over the phone within 48 hours and requested to complete. It is anticipated that each interview will last approximately 20 minutes. At the end of each interview, the interviewer will record a field note of the circumstances and events during the interview. All interviews will be digitally recorded and professionally transcribed by Landmark Associates Inc. for analysis.

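### Section E6 does not fix caregiver consent before randomisation or before the envelope is opened, so caregiver selection could depend on arm

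*Protocol*

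**What the plan says.** Section E6 sets out the visit as a narrative. The patient gives written consent and completes the baseline questionnaires. Next, "The patient will then be randomized to receive either the QPS", with the GIS as the alternative. A reading time is given: "It will take approximately 5 minutes to read through the QPS or GIS". The caregiver step appears after this. Caregivers who agree to take part "will also be asked to provide consent and will be given the same information material" that the patient has.

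Where several caregivers are eligible, "the one most involved in the patient's care, as determined by the patient, will be the first person to be approached". Replacement after a refusal again follows the patient's ranking: "If he/she declines to participate, the next most involved caregiver identified by the patient will then be approached", and so on down the list. Willingness is itself an eligibility condition: under Caregiver participation, a caregiver must be someone who "is willing to participate in the study and able to complete the questionnaires".

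Section E4 deals with concealment: "Both the QPS and GIS will be concealed in opaque envelopes that will be identical to each other". Research staff, patient and caregiver are all to be blinded to the contents.

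Secondary objective 2 (section A) compares caregivers' perception of helpfulness between the two sheets. Section F assigns it a two-sample t-test or Wilcoxon rank sum test. Up to 136 caregivers may be enrolled (E1), and their data are collected where available (F).

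**The concern.** Patients are randomised; caregivers inherit the patient's arm. The caregiver comparison has the protection of randomisation only if the set of caregivers who join would have been the same whichever sheet the patient drew. The simplest way to secure that is to settle who the caregiver is, and obtain consent, before allocation. E6 does not do this, and a coordinator following its text in order would approach caregivers when the patient already holds, and may have read, the sheet.

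There are two routes by which arm could then enter. The patient names the caregiver to be approached first and each replacement after a refusal, and may do so with the sheet in mind. The caregiver may decide whether to join after seeing or hearing about it. The two sheets are plainly different once read: section E8 describes one as a single page of 25 questions and the other as general information about palliative care. Neither route requires anyone to know which sheet is the active one.

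At stake are secondary objective 2 and the seven 0-10 caregiver ratings listed in E9. The planned test is unadjusted. The only caregiver form that E6 describes is completed after the visit, so no caregiver baseline measure is described that would show an imbalance.

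**Working it through.** The protocol gives no sample size, take-up rate or power for caregivers, so there is no caregiver figure to reproduce. The patient sample size in section F has no bearing on this point. The check is mainly one of reading the text.

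**Order of steps in E6**

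1. Patient consent, then baseline forms, then randomisation: these are linked by explicit time words.
2. Reading time for the sheet: a duration, with no statement of what must wait for it.
3. Caregiver consent and receipt of the sheet: one step, placed after 1 and 2, with no time word linking it to either.

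The narrated order therefore puts the caregiver step after allocation, but no sentence states this as a rule. Equally, no sentence requires the caregiver step to come earlier.

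**When the order matters**

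- Caregiver consented before randomisation: joining cannot depend on arm.
- Consented after randomisation with the envelope sealed: the arm is hidden from everyone present, so the expected difference in joining is still zero.
- Consented after the envelope is opened: joining can depend on the sheet.

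Only the third case is exposed, and the protocol does not exclude it.

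**Illustration of size (all inputs assumed, none from the protocol; no true effect of the sheet)**

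*Proportion agreeing with item 3.* Suppose 70% of caregivers join whichever sheet is drawn, and a further 15% join only with the QPS. Take-up is then 85% v 70%.

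QPS proportion = (0.70 × p + 0.15 × q) / 0.85, and GIS proportion = p, where p is agreement among those who always join and q is agreement among the extra joiners.

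- p = 0.70, q = 0.50: (0.490 + 0.075) / 0.85 = 66.5% v 70%, a spurious gap of 3.5 points.
- p = 0.80, q = 0.30: (0.560 + 0.045) / 0.85 = 71.2% v 80%, a spurious gap of 8.8 points.

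*Mean on a 0-10 scale.* Let take-up be a in one arm and b in the other (b > a), with the extra joiners differing by d points. The bias is d × (b − a) / b.

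- a = 0.60, b = 0.70: (0.10 / 0.70) × d = 0.14 to 0.43 for d = 1 to 3.
- a = 0.50, b = 0.70: (0.20 / 0.70) × d = 0.29 to 0.86 for d = 1 to 3.
- a = b = 0.70, with the same kind of caregiver joining: 0.

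**Set against sampling error.** If all 68 patients per arm had an eligible caregiver, take-up of 70% and 85% gives about 48 and 58 caregivers. The standard error of the difference in proportions is:

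- √(0.70 × 0.30 / 48 + 0.665 × 0.335 / 58) ≈ 9.1 points for the first example.
- √(0.80 × 0.20 / 48 + 0.712 × 0.288 / 58) ≈ 8.3 points for the second.

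The illustrated bias is thus roughly 0.4 to 1.1 standard errors. The direction is arbitrary: in these examples it runs against the QPS, and with extra joiners who are more favourable it would run the other way.

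**The case against.** The strongest reply is that the order is inferred. The caregiver sentence carries no time word, and the paragraph is not strictly chronological: the estimate of time for the questionnaires comes after randomisation, although the only questionnaires described to that point are completed before it. Figure 1, which summarises the design, is not shown and might settle the matter. This stands. A reader might infer that caregivers are in fact consented after randomisation and that the comparison has lost its randomised basis; the text does not establish either.

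Second, consent after allocation does no harm while the envelope is sealed. This also stands, and makes opening the envelope the critical moment. The text does not say that the caregiver is with the patient when it is opened, only that the caregiver accompanied the patient to the clinic. Nor does it say that the caregiver is approached first, so the route remains open.

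Third, who came to the clinic and who is most involved in care are settled before the visit, and the task asked of the caregiver is short. This narrows the scope for selection but does not remove it, since the ranking is the patient's statement and refusal is the caregiver's choice.

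Fourth, a reader might infer that nothing could be done in the analysis. That goes too far. Patient baseline data are collected, presence of a caregiver is a listed variable in E9, and take-up can be counted by arm. These allow a check and partial adjustment. They cannot reliably remove selection on caregiver traits that were not measured, and equal counts would not show that the same kind of caregiver joined.

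Finally, caregiver data are collected where available and carry no power claim. That limits the importance of the point but is no reason to leave the order open.

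**Conclusion.** The point holds as a gap in procedure. E6 does not fix caregiver identification and consent before randomisation or before the envelope is opened, and its narrated order places that step afterwards. Caregiver selection could therefore depend on arm, and the planned comparison makes no allowance for this.

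The effect is confined to secondary objective 2 and the other caregiver ratings. The primary patient comparison is untouched. The size of any bias cannot be derived from the protocol: it is nil if joining does not depend on arm, and the illustrated 4 to 9 percentage points, or 0.14 to 0.86 points on a 0-10 scale, rest wholly on assumed take-up and assumed differences between joiners. The case for acting is that the remedy is nearly free and that an analysis plan cannot later supply a caregiver group fixed before allocation.

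**What to change.** In E6, state that the caregiver is identified, approached and consented before the patient is randomised, including any replacement after a refusal. If that is not workable in clinic, the minimum is that this step is completed before the envelope is opened.

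Record for every patient whether an eligible caregiver was present, how many were approached and whether one consented, and report these counts by arm.

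The cost is a few minutes more before randomisation. Sample size and the primary analysis do not change. If the clinic already works in this order, one clarifying sentence in E6 and the counts by arm are enough.

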## **E7. Data Collection and coding**

The research nurse/research coordinator will review the patient's chart and collect information regarding diagnosis, demographics, and other patient characteristics (such as patient age, gender, race, cancer diagnosis, Edmonton Symptom Assessment System [ESAS] scores). The demographic and clinical characteristics will be obtained from either the patients' medical records or from the participant responses to the study assessment questionnaires that will be administered during the study. The transcribed consultation will be coded and pertinent information will be extracted by 2 trained coders who will be blinded to group allocation. The extracted information will include the type and category of each question asked such as the palliative care team/services provided, symptoms and treatment, prognosis, end of life issues, or other. Each coder will code all the transcripts and re-code a random 10% of their own initial work to determine intra-rater reliability,

and a random 10% of the other's work to determine inter-rater reliability.

